### Implementation trial

#### Study design

The implementation trial is conducted as a two-arm, cluster non-randomised controlled trial with a parallel process evaluation. For this, 12 health facilities (clusters) were allocated to the intervention (PDSA cycle) and comparison (usual strategy) sites (figure 1), based on logistics and interest in facility-level outcomes (SHP’s adherence to oral AZM administration according to protocol).^50^ The six intervention sites will use the PDSA cycles to co-design, refine and adapt context-specific implementation strategies to enhance SHP’s adherence to oral AZM as part of a sepsis prevention protocol for maternal sepsis during vaginal birth. The six comparison sites will implement oral AZM during vaginal birth using the usual strategy for adopting new treatments—a one-off training workshop and guideline distribution. Then, fidelity in healthcare facilities that used PDSA cycles to generate implementation strategies will be compared with those that used the usual strategy to understand which strategies work best and how they are effective in various settings.

#### Theoretical framework

The implementation trial is guided by two frameworks: the Consolidated Framework for Implementation Research (CFIR) and the Reach, Effectiveness, Adoption, Implementation and Maintenance (RE-AIM). CFIR, a determinant framework comprising 39 constructs across five domains (Innovation, Outer Setting, Inner Setting, Individuals and Implementation Process), was chosen to understand barriers and facilitators influencing the implementation of oral AZM and the implementation outcomes.^4651^,^53^ On the other hand, the RE-AIM was selected as the evaluation framework to assess individual-level (reach and effectiveness) and setting-level (adoption, fidelity and sustainability) outcomes.^54 55^

#### Study sites

Our trial is implemented in 12 purposively selected sites within six states from a pool of facilities where a pre-site readiness assessment was conducted to account for health systems-based organisation factors. The inclusion criteria were (1) facility level (primary, secondary and tertiary) and facility ownership: public (government-owned) and private (individual, charity, faith-based or non-government organisation-owned); (2) provision of maternity services (ANC, childbirth and postnatal care services); (3) mixture of high, medium and low number of vaginal births and (4) location (rural, semiurban and urban).

#### Study population

Our study population consists of (1) SHP (eg, midwives, nurses, obstetricians) providing care during vaginal birth and (2) pregnant women (see *Participant inclusion and exclusion criteria*) giving birth vaginally across the 12 sites.

#### Sample size

Given that our implementation study uses PDSA as an implementation strategy to (1) facilitate fidelity to AZM according to the protocol and (2) generate context-specific learnings to improve quality of care—not for generalisation—the conventional approach to calculating sample size is not required.^56^ Instead, we will monitor all vaginal births in the 12 facilities for 9 months to assess fidelity.

#### Blinding

Blinding SHP within the selected health facilities is not feasible because they are directly involved in implementing the strategies to improve fidelity.^57^

#### Intervention: deployment of PDSA cycles to generate context-specific implementation strategies

At the PDSA sites, we will establish a multidisciplinary team (MDT) comprising a facility manager or head of department/unit, SHP, pharmacists, data managers and a patient representative. These MDTs will co-design, test and adapt implementation strategies generated through PDSA cycles to improve adherence to the oral AZM protocol for vaginal births. We will implement the PDSA cycle for 12 months, which involves four 1-day quarterly learning sessions and three alternating action periods using facility-generated data. During the learning sessions, MDTs will co-design implementation strategies using facility-generated data, suggest indicators to assess their performance and develop testing plans while reviewing progress and highlighting best practices. The action periods allow for the implementation, iterative testing and refinement of the co-designed strategies while monitoring and assessing progress towards adoption based on lessons learnt from previous testing. Technical support is provided to the MDTs throughout, and the process is documented using a PDSA documentation template. The co-designed implementation strategies are tested and refined for 9 months (ie, the three action periods) within the intervention period.

#### Comparison: usual strategy

At the non-PDSA sites, SHP in the selected health facilities will implement oral AZM during vaginal births using the usual strategy, which typically includes a one-off training workshop and distributing guidelines for administering the new treatment.

#### Outcome measures

The primary outcome is fidelity, with secondary outcomes as adoption, reach, feasibility, acceptability and sustainability (table 4). Fidelity (ie, SHP’s adherence to oral AZM according to protocol) is operationalised as the proportion of vaginal births in which oral AZM was administered according to the protocol during vaginal birth, using data extracted from facility records and observations to ensure accuracy. Adherence to oral AZM per protocol is defined as having ≥70% of the essential components, based on evidence of <70% non-compliance with antepartum and intrapartum practice guidelines in Nigeria^58^ and other countries and disciplines.^59 60^

**Table 4 T4:** Implementation trial outcome, measure, data source and timeline

Outcomes	Measure	Data source	Timeline
Fidelity	The proportion of planned vaginal births in which oral AZM was administered according to the protocol/guideline	Health facility records and observation checklist	Midline and endline
	Factors influencing adherence to oral AZM administration according to the protocol	IDI with SHP	Endline
Reach	The proportion of eligible women who received oral AZM in planned vaginal delivery	Health facility records	Midline and endline
Adoption	SHP’s uptake of oral AZM in planned vaginal delivery as part of a sepsis prevention protocol	ORIC survey and KII with SHP and health facility managers	Baseline
	Factors that facilitated the adoption of oral AZM administration according to the protocol	IDI with SHP and health facility managers	Endline
Feasibility	The extent to which the implementation of oral AZM during planned vaginal delivery as part of a sepsis prevention protocol is considered feasible, given health facilities’ different needs and the availability and adequacy of required resources	KII with SHP and health facility managers	Baseline
		IDI with SHP and health facility managers	Endline
		Acceptability and feasibility of intervention measures, and FGD with MDT	Learning sessions 1 and 4
Acceptability	SHPs’ and women’s perception regarding administering and using oral AZM during planned vaginal delivery as part of a sepsis prevention protocol as agreeable, palatable or satisfactory	KII with SHP and health facility managers	Baseline
		IDI with SHP and women	Endline
Sustainability	The extent to which oral AZM during planned vaginal delivery becomes institutionalised as part of a sepsis prevention protocol	KII with health facility managers and SHP	Endline

AZM, azithromycin; FGD, focus group discussion; IDI, in-depth interview; KII, key informant interview; MDT, multidisciplinary team; ORIC, Organisational Readiness for Implementing Change; SHP, skilled health personnel.

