Beyond evidence on its effectiveness, there are also knowledge gaps regarding implementation. From an implementation perspective, the effective deployment of oral AZM for the prevention of maternal sepsis requires skilled health personnel’s (SHP’s) adherence to protocols in healthcare facilities.^36 37^ However, the typical top-down approach in Nigeria for guidelines or policy changes is to conduct a one-off training workshop and distribute the guidelines.^38^ This approach lacks evidence of sustained provider compliance, and no study has systematically evaluated implementation strategies to enhance SHP’s adherence to intrapartum AZM protocols in sub-Saharan settings. In addition, there is limited evidence on the facilitators, barriers and contextual factors influencing the implementation of oral AZM during vaginal birth to inform the design of context-specific implementation strategies and improve adherence.^23^ The Plan-Do-Study-Act (PDSA) cycle, a bottom-up approach, offers a promising strategy to develop, test and refine context-specific implementation strategies for the effective integration of evidence-based interventions, like intrapartum AZM prophylaxis, into routine practice in LMICs.^39^,^41^ Given the absence of AZM adoption in Nigeria for the prevention of maternal sepsis and uncertainty about effective implementation strategies,^42^ a systematic comparison of PDSA-generated strategies versus the usual strategy is needed to improve the fidelity of oral AZM in practice while upholding ethical standards and strategies to enhance SHP’s adherence across Nigeria’s health system and respecting the local medical context.

The AZIN-V trial is a hybrid type 2 effectiveness-implementation trial that simultaneously tests the clinical and cost-effectiveness of AZM while evaluating implementation. This study represents, to our knowledge, the first systematic evaluation of PDSA cycles for developing context-specific implementation strategies to enhance SHP’s adherence to intrapartum AZM protocols and would inform effective adoption and implementation in other comparable resource-constrained settings across Africa and beyond.

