#### Data collection methods

We will use quantitative and qualitative methods to assess the primary and secondary outcomes. Before the trial, we will assess the readiness of 12 healthcare facilities to adopt oral AZM during vaginal birth using the Organisational Readiness for Implementing Change (ORIC) validated survey.^61^ Using a semistructured interview guide, we will conduct key informant interviews to understand the barriers, facilitators and contextual factors influencing the implementation of oral AZM during vaginal birth in Nigerian health facilities guided by CFIR, as well as its feasibility and acceptability. We will also collect relevant contextual data, such as organisational characteristics, policy documents and healthcare system factors, to support exploring contextual factors. At the end of the PDSA cycles 1 and 4, we will use the validated 4-item scale: the Acceptability of Intervention Measure (AIM), the Feasibility of Intervention Measure (FIM)^62^ and focus group discussions using an open-ended semistructured discussion guide to collect data among the MDTs on the feasibility and acceptability of the co-designed implementation strategies. Data on fidelity are collected using facility records and an observation checklist deployed on REDCap. Additionally, we will conduct in-depth interviews (IDIs) at facilities with varying levels of adherence to the protocol to better understand the factors affecting fidelity and inform future improvements. Facility records will also be used to collect data on reach. Clinical data will not be collected from the implementation study sites.

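### Adoption is defined as staff uptake of azithromycin, but that uptake is assessed only at baseline, with a readiness survey and interviews

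*Protocol article*

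**What the plan says.** The implementation trial compares six sites using Plan-Do-Study-Act (PDSA) cycles with six using a one-off workshop and guideline distribution. Fidelity is the primary outcome and adoption is one of the secondary outcomes. Under Theoretical framework, adoption is listed among the setting-level outcomes and reach among the individual-level ones.

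Table 4 (Outcome measures) gives adoption two rows:

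- **Row 1.** The measure is skilled health personnel's "uptake of oral AZM in planned vaginal delivery as part of a sepsis prevention protocol". The source is "ORIC survey and KII with SHP and health facility managers". The timeline is baseline.
- **Row 2.** The measure is "Factors that facilitated the adoption of oral AZM administration according to the protocol". The source is in-depth interviews with personnel and managers. The timeline is endline.

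On the ORIC survey, Data collection methods states: "Before the trial, we will assess the readiness of 12 healthcare facilities to adopt oral AZM during vaginal birth". The Introduction describes the starting position in the country: "Given the absence of AZM adoption in Nigeria for the prevention of maternal sepsis".

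**The concern.** Uptake is something staff do once a treatment is available to them. Row 1 schedules its measurement before either implementation strategy has begun, and its survey instrument asks how ready an organisation is to change. A baseline value cannot depend on whether a site later used PDSA cycles or the usual workshop. A readiness score is also a different quantity from uptake, even where the two are related.

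A named secondary outcome is therefore at stake. A reader of the results would see an adoption finding that is really a readiness finding, and the report could not say how far staff took up azithromycin under either strategy.

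**Working it through.** No arithmetic applies, because the point rests on definitions and time points. The check sets the relevant entries side by side.

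1. **What is defined.** Table 4, adoption row 1: uptake of azithromycin by staff. This is actual use.
2. **What is measured, and when.** Same row: ORIC survey and key informant interviews, at baseline only. Data collection methods confirms that ORIC is given before the trial and concerns readiness. It describes the interviews as covering barriers, facilitators and context, together with feasibility and acceptability. It does not mention a level of uptake.
3. **What uptake could exist then.** The Introduction says azithromycin is not adopted in Nigeria for this purpose. Little or no uptake is therefore expected at the 12 sites at baseline. This is inferred from a national statement; the article gives no site data.
4. **Whether the later adoption row fills the gap.** Row 2, at endline, asks what facilitated adoption. It takes adoption as given and does not measure its extent.
5. **Whether another outcome fills it.** Reach is "The proportion of eligible women who received oral AZM in planned vaginal delivery", from facility records at midline and endline. Fidelity is the proportion of births in which azithromycin was given per protocol, from records and an observation checklist at the same two times. Both record real use, with the woman or the birth as the unit. A few staff could account for high reach while most had not taken up the practice, so neither gives staff uptake directly.
6. **Comparison within the table.** Feasibility and acceptability each have entries for the outcome itself at both baseline and endline. The uptake row has baseline alone.

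Count of time points for uptake under adoption: 1 before introduction, 0 after.

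**The case against.** The strongest reply has three parts.

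- **Azithromycin use is not unobserved.** All vaginal births in the 12 facilities are monitored for 9 months, and reach and fidelity are reported at midline and endline. A reader might infer from the adoption row that a large difference in use between strategies would go unseen. The article does not support that: such a difference would be expected to show in reach and fidelity, though per woman or per birth and not per provider. This part stands.
- **No comparison of adoption between arms is planned.** The only stated between-strategy model is for fidelity, and ORIC scores are analysed descriptively. So no invalid test is in prospect. This also stands, but a descriptive outcome still has to describe what its label says.
- **Adoption does have an endline entry.** True, but it covers factors only. The statement that adoption is measured only at baseline is correct for the uptake row, not for the outcome as a whole.

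Two wider inferences should not be drawn.

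- **Sustainability.** A reader might think it fails in the same way because it is assessed at endline of a supported period. Its stated measure is "The extent to which oral AZM during planned vaginal delivery becomes institutionalised as part of a sepsis prevention protocol", which endline interviews can address. The support in question ("Technical support is provided to the MDTs throughout, and the process is documented using a PDSA documentation template") is described only for the teams at the six PDSA sites, and endline is not dated relative to the end of that support.
- **Sustained compliance.** A reader might say that the Introduction's gap on sustained provider compliance goes unexamined. That remark concerns the one-off workshop approach. The comparison sites use that approach, and their fidelity is measured at midline and endline.

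**Conclusion.** The point holds for adoption alone. The uptake row pairs a measure of use with a readiness survey and interviews held before introduction, and no later adoption entry gives the level of uptake. As written, this secondary outcome would present readiness as uptake and could not describe adoption under either strategy.

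The size is modest. One secondary outcome of the non-randomised implementation component is affected. Fidelity, reach and the clinical trial are not. No numerical bias can be stated, because the plan would yield readiness scores and interview material, not an uptake proportion.

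The core conclusion rests on Table 4 and the description of ORIC in Data collection methods. Only the expectation of little or no uptake at baseline depends on the Introduction's national statement.

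**What to change.** In Table 4:

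- Relabel the baseline ORIC survey and key informant interviews as readiness to adopt.
- Add an adoption measure at midline and endline in all 12 sites, taken from the facility records and checklist already used for reach and fidelity. One suitable measure is the month in which each facility first gave azithromycin. Where records identify the provider, add the proportion of labour-ward skilled personnel who gave it to at least one eligible woman in the period.
- Keep the endline interviews on facilitating factors as they are.

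The cost is a small amount of extra extraction. The per-provider proportion depends on records naming who gave the drug, which the article does not state. If they do not, the month of first use is the facility-level fallback, and reach and fidelity can be cross-referenced for the amount of use.

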#### Data collection methods

We will use quantitative and qualitative methods to assess the primary and secondary outcomes. Before the trial, we will assess the readiness of 12 healthcare facilities to adopt oral AZM during vaginal birth using the Organisational Readiness for Implementing Change (ORIC) validated survey.^61^ Using a semistructured interview guide, we will conduct key informant interviews to understand the barriers, facilitators and contextual factors influencing the implementation of oral AZM during vaginal birth in Nigerian health facilities guided by CFIR, as well as its feasibility and acceptability. We will also collect relevant contextual data, such as organisational characteristics, policy documents and healthcare system factors, to support exploring contextual factors. At the end of the PDSA cycles 1 and 4, we will use the validated 4-item scale: the Acceptability of Intervention Measure (AIM), the Feasibility of Intervention Measure (FIM)^62^ and focus group discussions using an open-ended semistructured discussion guide to collect data among the MDTs on the feasibility and acceptability of the co-designed implementation strategies. Data on fidelity are collected using facility records and an observation checklist deployed on REDCap. Additionally, we will conduct in-depth interviews (IDIs) at facilities with varying levels of adherence to the protocol to better understand the factors affecting fidelity and inform future improvements. Facility records will also be used to collect data on reach. Clinical data will not be collected from the implementation study sites.

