**Methods and analysis:**

This is a multicentre hybrid type 2 trial conducted in six Nigerian states: Ebonyi, Edo, Gombe, Kano, Kwara and Lagos. The study aims to simultaneously test the clinical and cost-effectiveness of AZM (clinical trial) and the impact of implementation strategies (implementation research) in Nigeria’s unique healthcare context. The clinical trial is a two-arm, cluster-randomised controlled trial conducted across 48 health facilities, randomly assigned (1:1) to either intrapartum administration of oral AZM (intervention group) or usual care—the current routine practice (control group). A total of 5040 study participants (2520 in each group) will be enrolled in the clinical trial. The implementation trial is a two-arm cluster non-randomised controlled trial conducted in 12 health facilities (1:1) allocated to either a bottom-up approach using the Plan-Do-Study-Act cycle or a usual top-down approach with a one-time training workshop and distribution of clinical guidelines, with both arms administering oral AZM during vaginal birth while assessing fidelity (primary outcome).

For the clinical trial, data will be analysed using intention-to-treat statistical methods. The cost-effectiveness outcome will be analysed using the Incremental Cost-Effectiveness Ratio. Implementation outcomes will be analysed using descriptive statistics and a thematic approach.

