### Sites

From the six states, 48 health facilities are included in the clinical trial. The implementation trial will include 12 health facilities from the six states. Sites will only participate in either the clinical or the implementation trial. Study sites are selected based on their state-level location to avoid serving the same geographic clusters or communities, thereby reducing the risk of cluster contamination. The selection process will ensure a within-state comparison across various levels of healthcare (primary, secondary and tertiary) and facility types: public (government-owned) and private.

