### Adverse drug event monitoring

Adverse events (AEs), including serious AEs (SAEs), are closely monitored and recorded on the electronic case report form throughout the duration of the trial, in accordance with Good Clinical Practice guidelines and all applicable regulatory requirements. At each study visit, participants are evaluated for AEs and asked about any symptoms that have occurred between study visits. Participants are advised and requested to report symptoms suggestive of AEs. An AE is defined as any unfavourable or unintended medical occurrence in any participant who has received the trial drug or usual care, regardless of whether it has a causal relationship with the intervention. SAE is defined as any event that (1) results in death; (2) is life-threatening; (3) requires hospitalisation or prolongation of existing hospitalisation; (4) leads to persistent or significant disability or incapacity or (5) constitutes a congenital anomaly/birth defect. AEs are documented according to the severity, duration, grade, relationship to trial drugs, interventions given and outcome. The costs of treating all adverse drug events related to trial drugs will be borne by the trial. Each AE/SAE is assessed by the site investigator for severity, expectedness and its relationship to the trial drug or study procedure (unrelated, unlikely related, possibly related, probably related or definitely related). All SAEs are reported to the Principal Investigator, who will, in turn, notify the trial sponsor and the Institutional Review Board/ethics committee in accordance with local regulatory requirements. Any serious, unexpected adverse drug reactions will also be reported promptly to the national drug regulatory authority in line with pharmacovigilance requirements. All study participants with AEs are managed and followed up until the resolution or stabilisation of the AE. Where necessary, additional medical information is obtained to ensure a comprehensive evaluation of the AE. Safety oversight during the trial is provided by a Data and Safety Monitoring Board (DSMB) and other independent safety monitors.

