### Ancillary and post-trial care

All participants are covered by clinical trial insurance in case of serious adverse drug events arising from the use of trial drugs. There are no specific plans for post-trial care.

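### Twelve implementation sites give the study drug under a blanket exclusion of clinical data, which conflicts with the protocol's own adverse-event, DSMB and insurance provisions

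*Protocol article*

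**What the plan says.** The implementation trial compares two ways of introducing the drug, so both of its arms administer azithromycin (Abstract, Methods and analysis; Implementation trial, Study design). Its women are those "giving birth vaginally across the 12 sites", with a cross-reference to the clinical trial's inclusion and exclusion criteria (Implementation trial, Study population). The facilities are distinct from the 48 in the clinical trial: "Sites will only participate in either the clinical or the implementation trial" (Sites). On observation there, "we will monitor all vaginal births in the 12 facilities for 9 months to assess fidelity" (Implementation trial, Sample size). The data sources are facility records, an observation checklist, surveys and interviews, and no outcome in Table 4 concerns safety. Data collection methods closes with: "Clinical data will not be collected from the implementation study sites".

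Three other sections are worded more broadly:

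- **Adverse drug event monitoring** says that adverse events, serious ones included, are "closely monitored and recorded on the electronic case report form throughout the duration of the trial". Its definition of an adverse event covers a participant given either the trial drug or usual care, whether or not the event is causally related.
- **Research governance** makes the DSMB responsible for monitoring every SAE.
- **Ancillary and post-trial care** says: "All participants are covered by clinical trial insurance in case of serious adverse drug events arising from the use of trial drugs".

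**The concern.** The study itself creates the exposure at these 12 sites: the Introduction notes that azithromycin has not been adopted in Nigeria for preventing maternal sepsis. The exclusion of clinical data carries no qualification, and in ordinary usage clinical data include adverse events. Followed as written, it leaves women given the study drug at these sites with no planned SAE capture, while other sections read as though every exposed participant were covered.

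Two things are at stake. The first is oversight. Clinical-trial participants take the drug under a research nurse's eye and have visits at 3 days and at 2, 4 and 6 weeks, and nothing comparable is described for the 12 sites. The eligibility criteria exclude women with macrolide allergy or known cardiac disease. If screening failed at an implementation site, no planned data item would record the harm. The second is detection of rare serious events, where the number of women observed matters most.

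**Working it through.** **1. The plan's own exposure figure.** The Sample size section gives 2,520 women per group, for 6.5% versus 3.25%, 90% power, 5% significance, an ICC of 0.011, 20% loss and about 105 women per facility.

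- Individually randomised size by the standard two-proportion formula: 921 per arm.
- Design effect: 1 + (105 − 1) × 0.011 = 2.144, giving 921 × 2.144 = 1,975.
- Allowance for loss: 1,975 / 0.80 = 2,469, which is 2.0% below 2,520.
- Check on the total: 48 × 105 = 5,040 = 2 × 2,520.

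The figure reproduces closely enough, and 2,520 is used below as the number given azithromycin in the clinical trial.

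**2. Exposure at the 12 sites.** The article states no figure, so one has to be assumed:

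E = 12 × births per site per month × months × uptake; share = E / (E + 2,520).

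- *Months:* 9, the stated monitoring period.
- *Births:* 20 per month is the average volume in the site eligibility criterion, which applies to both trials. The 12 sites are a mix of high, medium and low volume with no counts given. The upper value of 50 is an assumption.
- *Uptake:* the fraction of vaginal births in which the drug is given. Reach is an outcome in Table 4 with no planned value, so 50% to 100% is an assumption.

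| Births/site/month | Uptake | E | Share |
|---|---|---|---|
| 20 | 50% | 1,080 | 1,080/3,600 = 30.0% |
| 20 | 70% | 1,512 | 1,512/4,032 = 37.5% |
| 20 | 100% | 2,160 | 2,160/4,680 = 46.2% |
| 50 | 50% | 2,700 | 2,700/5,220 = 51.7% |
| 50 | 70% | 3,780 | 3,780/6,300 = 60.0% |
| 50 | 100% | 5,400 | 5,400/7,920 = 68.2% |

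**3. Sensitivity.** The PDSA section says "We will implement the PDSA cycle for 12 months". Applying 12 months to all 12 sites at 20 births and full uptake gives 2,880, or 53.3%. At 20 births, 9 months and only 30% uptake, E is 648 and the share 20.5%. A share of exactly one half needs 2,520 / (12 × 9) = 23.3 births per site per month at full uptake.

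**4. The provisions side by side.**

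| Provision | Scope as worded | Means at the 12 sites |
|---|---|---|
| Adverse-event definition | any participant given the trial drug | case report form and study visits, neither described there |
| DSMB remit | all SAEs | no planned source of SAEs |
| Insurance | all participants | no planned record of events |
| Implementation data | no clinical data | facility records and checklist, for fidelity and reach |

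The first three rows include women at the 12 sites on a literal reading. The fourth rules out the data on which the first two depend.

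**The case against.** The strongest reply is that the adverse-event section sits among the clinical-trial methods, before the implementation trial is introduced. Its machinery (case report form, study visits, site investigator) belongs to the 48-site trial, and the DSMB's review by masked treatment group also fits that trial. The exclusion closes an account of how fidelity, reach, feasibility and acceptability are measured, and may mean only that clinical outcomes are not collected. The article condenses a fuller protocol that may set out SAE reporting for these sites.

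Part of this stands. The article does not forbid SAE or spontaneous reporting at the 12 sites, so a reader should not infer that a serious reaction there could never reach the principal investigator, the DSMB or the regulator. But the objection does not remove the conflict. This is an unqualified statement set against broader ones, not a detail left out. If the full protocol captures SAEs there, the sentence is worded wrongly; if it does not, oversight has a gap.

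Other inferences go too far:

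- *Close to half of exposed women yield no safety information.* The 46% needs 20 births a month at every site and full uptake, neither of which the article states for these 12 sites.
- *The insurance cannot operate.* A claim can start with the woman or her facility and does not depend on research data.
- *The safety objective is compromised.* That objective compares azithromycin with usual care. The 12 sites are non-randomised, have no untreated arm and cannot inform it.
- *Adding these women would tighten the upper bound on a serious event rate with no events seen from 3/2,520 = 1.2 to 3/4,680 = 0.64 per 1,000.* That treats passive records as complete detection. Even in the clinical trial, the planned 20% loss leaves 2,016 women and 3/2,016 = 1.5 per 1,000.
- *All 12 sites are less supervised.* The six PDSA sites have multidisciplinary teams and continuing technical support.

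**Conclusion.** The point holds as an internal conflict with a consequence for participant safety. As worded, women given the study drug at 12 separate sites have no planned safety data, although the adverse-event definition, the DSMB's remit and the insurance statement all extend to them. The number affected is unknown. It is about 1,080 to 5,400 women, or 30% to 68% of all azithromycin exposures, if volume is 20 to 50 births per site per month, uptake 50% to 100% and the period 9 months. Volume and uptake are assumptions, and lower uptake would bring the share down. Even 1,080 women is a large group beside 2,520.

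The between-arm safety estimate, the sample size and the primary analyses are not affected. What is lost is oversight of exposed women and some ability to notice rare serious events. The sponsor should correct this, but it does not threaten the trial's main result.

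**What to change.** Reword the closing sentence of the implementation trial's Data collection methods along these lines: *No efficacy outcomes are collected at implementation sites. Serious adverse events and suspected adverse drug reactions in women given azithromycin, and in their newborns, are recorded when found in the facility records reviewed for the study or reported by facility staff. They are reported by the route described under Adverse drug event monitoring and summarised descriptively for the DSMB, separately from the randomised comparison.* Then align the adverse-event, Research governance and insurance sections, so that each says whether it covers the 12 sites. If the full protocol already provides for such reporting, only the wording needs correction.

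The cost is modest: extra work in a record review already planned for all vaginal births, and staff briefing on SAE reporting. The article does not say that a checklist is completed from records for each birth, so the new items should be attached to the record review. The main limitation is that capture would be passive and incomplete. The summary should say so, and should not pool these women with the actively followed ones to claim an upper bound on event rates. Design, sample size and primary analyses stay as they are.
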